##### Trial status

The study has ethical approval from the Human Research Ethics Committees of Monash University and the University of Newcastle. The trial has been registered as a trial at the Australian New Zealand Clinical Trials Registry (ANZCTR) registration number ACTRN 12611000553976 at http://www.ANZCTR.org.au/ACTRN12611000553976.aspx. To date, the baseline measurement phase of the trial has been completed and the intervention phase is nearing completion.

## Discussion

The study methodology will deliver a community-level estimate of the effectiveness of a practice-change intervention for diabetes, providing valuable information regarding the implementation of large-scale strategies for practice change.

### Challenges and limitations

There were a number of challenges to consider in the execution and analysis of this type of study. Below is a description of some of the major challenges and how they were managed.

### Definition of a type 2 diabetes ‘case’

A study case was defined as having either a single HbA1c test where the result was greater than 7%, or two HbA1c tests within the study period. This approach was used to exclude those cases where a single HbA1c test had been used to screen for diabetes. While this criterion resulted in the omission of some cases of diabetes (*i.e.*, those who had not had an HbA1c test), the scale of the study and avoidance of participant bias was considered to compensate for any potential impact on generalizability of results. Some individuals may travel, receiving their care from specialists outside the selected communities. However, any such effect is likely to be similar across experimental and control communities.

### Use of the HbA1c test as a screening tool

The HbA1c test was not recommended as a screening test in Australia at the time of study commencement and does not attract Medicare reimbursement when used as a diagnostic test. Individuals with only one HbA1c test where the test result is below 7% will be excluded from the sample. Therefore, should the use of the HbA1c test as a screening tool have increased during the study period, it is unlikely to influence the study outcome. Should such a change occur, it will be possible to assess using interrupted time series analysis whether an overall increase in the use of one-off HbA1c tests has occurred over time, because the study data on HbA1c testing will provide a near-complete record of all HbA1c testing in the study communities over the five-year study period.

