### Selection of case sample

For the two-year baseline period, the two pathology companies used the postcode of the treating doctor to identify the potential cases in each study town. The existence of at least one HbA1c test was the criterion for an individual to be identified as a potential case of diabetes. A study case was defined by having either a single HbA1c test where the result was greater than 7%, or two HbA1c tests within the study period. This approach was used to exclude those cases where a single HbA1c test had been used to screen for diabetes. This criterion may have resulted in the omission of some cases of diabetes (*i.e.*, people with diabetes who had not had an HbA1c test). However, more serious forms of bias are avoided, because neither provider consent nor patient consent was required.

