### Data extraction procedure

For each case the following de-identified unit record data were extracted from pathology laboratory records: date of birth, gender, de-identified doctor code, postcode of doctor’s clinic, postcode of patient, date and value of each HbA1c test, date and value of each cholesterol test, date and value of each triglycerides test, date of each HDL cholesterol test, date and value of each LDL cholesterol test, and date of each urinary albumin test. The unit record data were extracted for three time periods: pre-test measures were taken over the 24 months prior to the intervention retrospectively; during the intervention, measures were collected prospectively; post-test measures will be taken in the 24 months following the termination of the intervention. Where both pathology companies operate in the same town, the two separate data sets will be combined to produce a single data set for each town.

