### Measures

#### Primary outcome

##### Glycaemic control

The incidence and progression of complications of diabetes are reduced for people with lower HbA1c [8-10]. Therefore, guidelines recommend an overall target of ≤7.0% for HbA1c [6]. Using the most recent HbA1c for each case within each 24-month timeframe, the mean HbA1c across the town, and the proportion of all cases whose most recent HbA1c value is ≤7.0%, was determined.

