##### Statistical methods

Changes in the proportion of patients in each town exhibiting glycaemic control, appropriate frequency of testing for each of HbA1c, blood lipids, urinary albumin, and control of lipids and albumin will be assessed at baseline and post-test as described in the measures section. Analysis of the predictors of metabolic control, using age and gender will also be assessed. Analyses using cluster-level summaries are more robust than analyses based on individual-level data when there are fewer than 15 clusters per treatment arm [35]. Therefore, the primary outcome for this study will be analysed by calculating the proportion of subjects with a HbA1c level below 7% within each cluster and then comparing the proportion of the intervention group with the proportion of the control group using a two sample t-test. The main analysis will be conducted with all the available data using the intention-to-treat principle. Subgroup analyses will be conducted by gender and age group. A similar approach will be used to test the secondary outcomes.

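### The check on HbA1c screening follows an overall trend in one-off tests, but what could bias the primary comparison is a between-arm difference in who becomes a case

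*Protocol article*

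**What the plan says.** Under *Use of the HbA1c test as a screening tool*, the protocol article considers that screening with HbA1c may have grown during the study. It gives one reason not to worry, "Individuals with only one HbA1c test where the test result is below 7% will be excluded from the sample", and concludes that "it is unlikely to influence the study outcome". The one quantity it proposes to examine is "whether an overall increase in the use of one-off HbA1c tests has occurred over time". That check is worded conditionally: "Should such a change occur, it will be possible to assess using interrupted time series analysis". No comparison by arm is mentioned.

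*Selection of case sample* defines a case as "either a single HbA1c test where the result was greater than 7%, or two HbA1c tests within the study period", and the discussion section on the definition of a case repeats this. The primary outcome under *Glycaemic control* includes "the proportion of all cases whose most recent HbA1c value is" at or below 7.0%. *Statistical methods* analyses it by "comparing the proportion of the intervention group with the proportion of the control group using a two sample t-test".

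The intervention components include town-level feedback on testing at the recommended frequency and a per-GP comparison on the same measure. The section on variation between guidelines says that the learning module and the feedback concentrated on six-monthly HbA1c testing. Control towns receive nothing from the research team.

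**The concern.** The denominator of the primary outcome depends on how often people are tested. Someone with a single result at or below 7% is not a case, but a second test makes that person a case, and a controlled one if the latest result is again at or below 7%. A single result above 7% also makes a case, an uncontrolled one. The exclusion cited as reassurance closes neither route.

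Because the analysis compares arms, a change in case entry common to both arms largely cancels. A change in one arm does not, and it would alter the proportion controlled with no change in care. A trend in one-off tests over the whole study cannot separate these situations. It could even point the wrong way: if the intervention prompts second tests, some people move out of the one-off group and into the case group, so one-off tests fall while controlled cases rise.

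**Working it through.** **Inputs from *Sample size*.** Average town 20,000 people, 2.9% treated for diabetes, 14 towns, 50% controlled under usual care, target difference 10 points.

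**The plan's own figures.** 20,000 × 0.029 = 580 cases per town, and 14 × 580 = 8,120, as stated. The design effect is 1 + (464 − 1) × 0.015 = 7.945, and 2 × 408 × 7.945 = 6,483, close to the stated 6,490. The point made here changes none of these.

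**Which people reach the denominator under the case definition.**

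| Tests in the period | Case? | Effect on proportion controlled |
|---|---|---|
| One, at or below 7% | No | None |
| One, above 7% | Yes | Lowers it |
| Two or more, all at or below 7% | Yes | Raises it |

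The first row is the group whose exclusion supports the reassurance. It contributes zero under any split between arms. The other two rows can carry bias, in opposite directions.

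**Size, as an illustration.** The documents give no rate of screening or of extra case entry, so the following is assumed. Let *e* be the extra cases as a share of existing cases, and *c* the share of them whose latest HbA1c is at or below 7%. Without any true effect, the proportion controlled becomes (0.5 + *e* × *c*) / (1 + *e*).

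For one town of 580 with 290 controlled (50%):

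- *e* = 5% (29 extra cases): all uncontrolled, 290/609 = 47.6%; all controlled, 319/609 = 52.4%. Shift −2.4 to +2.4 points.
- *e* = 10% (58 extra cases): all uncontrolled, 290/638 = 45.5%; all controlled, 348/638 = 54.5%. Shift −4.5 to +4.5 points.
- Even mix, *c* = 0.5: (0.5 + 0.5*e*) / (1 + *e*) = 0.5. Shift zero.

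**What an overall trend can show.** Hold the overall rise in cases at 5%, assume arms of equal size, and vary only the split between intervention and control:

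| Split (intervention/control) | Spurious difference, *c* = 1 | *c* = 0.8 | *c* = 0 |
|---|---|---|---|
| 5% / 5% | 0 | 0 | 0 |
| 7.5% / 2.5% | +2.3 | +1.4 | −2.3 |
| 10% / 0% | +4.5 | +2.7 | −4.5 |

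For example, 10%/0% with *c* = 0.8 gives (0.5 + 0.08)/1.10 = 52.7%, against 50%. The same overall rise fits a difference of zero or of several points. An overall trend in cases would therefore not reveal the bias, and a trend in one-off tests is a further step away.

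**The case against.** Several points on the other side stand.

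- **The check gates nothing.** It appears among the limitations, is worded as a possibility, and has no decision rule attached. A reader might infer that it would clear or condemn the primary result; the document does not say so, and the primary analysis does not depend on it.
- **Pooling of the arms is not stated.** The check answers a question about secular change, and the doctor's postcode is in the extract, so a split by arm is available. But the quantity named is an overall increase in one-off tests, and even a split of that series would miss case entry.
- **The intervention is not described as promoting screening.** The feedback and the six-month interval concern monitoring of known patients, and the article notes that diagnostic use is not reimbursed. A reader might infer a documented screening effect; there is none. What is documented is promotion of test frequency in one arm only, which could change who reaches two tests.
- **The illustration uses corner cases.** It puts all extra entry in one arm. Its range is symmetric about zero, so it fixes neither size nor direction.
- **The series may be buildable.** *Data extraction procedure* reads "For each case the following de-identified unit record data were extracted from pathology laboratory records", which might suggest that one-off tests at or below 7% are absent. Yet *Selection of case sample* treats anyone with one HbA1c test as a potential case, and the screening section describes a nearly complete record of testing. The wording is ambiguous; it does not show that the series cannot be built.

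It can also be said that the root of the problem is the case definition. That is fair, but the reassurance and the check are separate statements, and following them as written would leave a biasing arm difference undetected.

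**Conclusion.** The point holds in a limited form. That screening is unlikely to influence the outcome does not follow from the case definition, and the one check offered tracks a quantity that cannot show the relevant bias. Whether any bias exists, how large it is and which way it runs cannot be known from the document. Under assumed extra entry of 5% to 10% in one arm from a base of 50% controlled, the shift is at most about 2.4 to 4.5 points either way against a 10-point target, and zero with evenly mixed entrants. It would be wrong to conclude that the primary result is biased, or biased in favour of the intervention. This should be changed because the better check is cheap and its core uses case records that the plan already extracts.

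**What to change.** 1. Compare by arm and period, at town level, the number of cases and of new cases, split by entry route: a single test above 7%, and two or more tests all at or below 7%. Report the arm difference with a confidence interval, since with so few towns a non-significant result alone is weak reassurance.
2. Add a sensitivity analysis of the primary outcome restricted to people who were already cases at baseline, where records can be linked across periods.
3. Make the statement that screening is unlikely to influence the outcome conditional on finding no arm difference in step 1.
4. Reconcile *Selection of case sample*, *Data extraction procedure* and the screening section on whether records cover everyone with at least one HbA1c test or only study cases. A series by arm of one-off tests at or below 7% is optional and depends on the answer. If only cases were supplied, the completed baseline data lack those tests too, and changing the post-test extraction alone would leave the series without a pre-intervention segment. Steps 1 to 3 need case records only.

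The cost is a little extra analysis and some rewording. The sensitivity analysis leaves out newly diagnosed people, so it supplements the main analysis and does not replace it.

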### Variation in pathology assay techniques and instrumentation

HbA1c analysis results are subject to variation as a result of the type of equipment used, with the analysis method accounting for differences of up to 23% in the result [36,37]. In the course of this study, changes in the equipment and methods used for HbA1c analysis were monitored via communication with the two pathology companies to assess the need for sensitivity analyses exploring the size of any such effect.

### Variation between guidelines on HbA1c test frequency

Both the NHMRC and Royal Australian College of General Practitioners (RACGP) have guidelines on diabetes management. The NHMRC is the national body that provides authoritative, evidence-based national guidelines on a wide range of health matters. The RACGP guidelines are designed specifically for the general practice setting and are available in a handbook along with a full range of matters relevant to general practice. The NHMRC guidelines stated that HbA1c testing should occur every six months [38]. While the RACGP guidelines nominated six-month testing of HbA1c, the document had a focus on the 12-month cycle of care and the associated government funding for annual testing [13]. While the ALM and the feedback to GPs focused on the six-month interval, it is possible that GPs may have placed more weight on the 12-month interval. Therefore, analyses will address both six-month and 12-month intervals for HbA1c testing.

### Pathology testing occurring outside the participating pathology companies or towns

Although considerable efforts have been made to include only towns where the two participating pathology companies provided the vast majority of pathology services, it is possible that in some towns a small proportion of pathology testing may have occurred at other locations. For example, some pathology testing may have been sent to hospitals in larger towns nearby. At regular intervals during the course of the study, a sample of GPs were asked by telephone where they sent their pathology in order to assess whether this was occurring. It was also possible that individuals may on occasion have travelled to other towns for testing.

### Matching and merging records for de-identified patient data across pathology companies

The two pathology companies independently provided de-identified unit record data for each ‘case’. Therefore, the data was obtained as two independent data sets that were merged to provide a profile for all individuals in each town. Gender and date of birth were used to identify any individual who may occur in both datasets and data was merged for that individual.

### Individuals may move into or out of the dataset over time due to death, geographical re-location, or initial diagnosis

The data were analysed on the assumption that individuals entering or leaving a town would occur at a reasonably constant rate in each town. These effects would be expected in equal proportions across the intervention and control towns.

### Standard population guidelines may not be appropriate for all cases

Higher cut-off points for glycaemic control (*e.g.*, 8% for HbA1c in older patients) may be recommended in some cases. The primary outcome analysis relates to changes in mean HcA1c levels and would, therefore, be relatively unaffected by this factor. Analyses relating to the proportion of cases in each town achieving glycaemic control may require analyses to apply varying cut points with respect to age, however this does introduce an additional element of arbitrariness with respect to which age cut-offs are used.

### Pathology testing data provides a limited indicator of quality of diabetes care

The breadth and depth of best-practice diabetes care cannot be measured by focusing solely on pathology-based tests. There are a number of aspects of quality diabetes care, which although important, cannot be measured within the scope and focus of this study

### Participation rates

Poor participation rates are common in GP research [39,40]. The study will implement a range of evidence-based strategies to increase participation. It should be noted that because the outcome measures are population based, even if participation is poor, the study will provide a ‘real world’ indication of the impact of these sorts of methods, given that the intervention components reflect best practice in CME.

## Conclusions

Despite the identified methodological challenges, the study data are likely to provide valuable information regarding monitoring and improvement of healthcare using ongoing administrative data sets at a population level. The study also has potentially wide-reaching applications for evaluating guideline adoption free from bias associated with provider and participant non-consent.

## Abbreviations

CME: Continuing medical education; NHMRC: National Health and Medical Research Council; ALM: Active learning module; RACGP: The Royal Australian College of General Practitioners; QI: Quality improvement; CPD: Continuing professional development; GP: General practitioner; NSW: New South Wales.
